## Abstract

**Abstract:**

**Introduction:**

HIV drug resistance poses a challenge to the United Nation’s goal of ending the HIV/AIDS epidemic. The integrase strand transfer inhibitor (InSTI) dolutegravir, which has a higher resistance barrier, was endorsed by the WHO in 2019 for first-line, second-line and third-line antiretroviral therapy (ART). This multiplicity of roles of dolutegravir in ART may facilitate the emergence of dolutegravir resistance.

**Methods and analysis:**

Nested within the International epidemiology Databases to Evaluate AIDS (IeDEA), DTG RESIST is a multicentre study of adults and adolescents living with HIV in sub-Saharan Africa, Asia, and South and Central America who experienced virological failure on dolutegravir-based ART. At the time of virological failure, whole blood will be collected and processed to prepare plasma or dried blood spots. Laboratories in Durban, Mexico City and Bangkok will perform genotyping. Analyses will focus on (1) individuals who experienced virological failure on dolutegravir and (2) those who started or switched to such a regimen and were at risk of virological failure. For population (1), the outcome will be any InSTI drug resistance mutations, and for population (2) virological failure is defined as a viral load >1000 copies/mL. Phenotypic testing will focus on non-B subtype viruses with major InSTI resistance mutations. Bayesian evolutionary models will explore and predict treatment failure genotypes. The study will have intermediate statistical power to detect differences in resistance mutation prevalence between major HIV-1 subtypes; ample power to identify risk factors for virological failure and limited power for analysing factors associated with individual InSTI drug resistance mutations.

**Ethics and dissemination:**

The research protocol was approved by the Biomedical Research Ethics Committee at the University of KwaZulu-Natal, South Africa and the Ethics Committee of the Canton of Bern, Switzerland. All sites participate in International epidemiology Databases to Evaluate AIDS and have obtained ethics approval from their local ethics committee to collect additional data.

**Trial registration number:**

NCT06285110.

STRENGTHS AND LIMITATIONS OF THIS STUDYDTG RESIST is a large international study of dolutegravir resistance in individuals experiencing virological failure on antiretroviral therapy (ART) in diverse settings in sub-Saharan Africa, Asia and Latin America.Sanger and whole genome sequencing will be performed in regional laboratories in Mexico, South Africa and Thailand.Genome-Wide Association Study methods, Bayesian evolutionary models and phenotypic testing will explore and predict treatment failure genotypes and their clinical relevance.A limitation is the absence of genotypic resistance data from participants before they started dolutegravir-based ART.The distribution of HIV-1 subtypes across participating sites is uncertain, and the statistical power of some comparisons of drug resistance mutations will be limited.

## Introduction

 The emergence of HIV drug resistance threatens the United Nations’ goal of ending the HIV/AIDS epidemic by 2030.^1^,^3^ HIV drug resistance has increased substantially with the expansion of access to antiretroviral therapy (ART) in low-income and middle-income countries.^4 5^ The regimen used widely in recent years combined the nucleoside reverse transcriptase inhibitors (NRTIs) tenofovir and emtricitabine with the non-NRTI (NNRTI) efavirenz and thus contained three drugs with a low genetic barrier to resistance. As a result, acquired dual-class NRTI and NNRTI resistance was detected in many people living with HIV (PWH) who experienced virological failure on this regimen.^4^ There has also been a steady increase in pretreatment drug resistance (PDR). By 2016, NNRTI PDR exceeded 10% in Southern and Eastern Africa and approached this level in Latin America and the Caribbean. The 10% NNRTI PDR threshold is the point at which the WHO recommends a change in the standard first-line ART regimen.^6 7^

As a response to the high levels of resistance, WHO endorsed the integrase strand transfer inhibitor (InSTI) dolutegravir in 2019 as the primary choice for both first-line and second-line ART across all groups, including pregnant women and those who may become pregnant.^8^ By mid-2022, over 100 countries had incorporated dolutegravir into their treatment guidelines.^9^ Dolutegravir has a high genetic barrier to resistance,^10 11^ and thus far, only a few people with HIV (PWH) have been found to develop resistance to it.^12^,^14^ The types of mutations that cause dolutegravir resistance may vary by treatment history and HIV-1 subtype. For example, the Arg263Lys mutation appears to be relatively more common in PWH who had not previously received first-generation InSTIs than in those previously exposed to INSTIs.^15^ The Gln148His/Lys/Arg mutation may be less common in subtype C than in other subtypes.^16^

The risk factors and mutation patterns contributing to dolutegravir resistance are not as well defined as those for older antiretroviral drugs. Dolutegravir’s extensive use in areas with limited resources, where treatment options are more uniform, the reuse of drugs is common and access to adherence support, viral load (VL) and resistance testing may be limited, could facilitate the emergence of resistance mutations. The Dolutegravir Resistance (DTG RESIST) study aims to document the resistance patterns and contexts in which dolutegravir resistance emerges and thus contribute to safeguarding the long-term sustainability of the global HIV response. DTG RESIST has two parts. The first is a collaborative analysis of existing data from HIV cohort studies, which has recently been published.^15^ Here, we describe the second part of the study, which prospectively recruits PWH who experience virological failure on dolutegravir-based ART in 17 countries in sub-Saharan Africa, South and Central America, and Asia.

## Study aims and hypotheses

The prospective part of DTG RESIST has three aims:

In aim 1, we examine viral sequences to determine the prevalence and patterns of dolutegravir resistance in adults and adolescents living with HIV-1.In aim 2, we combine the HIV drug resistance data from aim 1 with clinical and programmatic data collected within the International epidemiology Databases to Evaluate AIDS (IeDEA) network to explore the factors associated with emergent dolutegravir resistance.In aim 3, we characterise the phenotypic effect of novel drug resistance mutations (DRMs) or novel combinations of mutations and explore the mutational pathways of dolutegravir resistance across HIV-1 subtypes.

We hypothesise that the prevalence and spectrum of InSTI DRMs will differ by HIV-1 subtype and by treatment context (aim 1); that NRTI resistance, previous exposure to InSTI drugs, male sex, younger age, second-line or third-line ART or advanced disease, exposure to rifampicin and lack of routine VL monitoring are risk factors for virological failure and the development of dolutegravir resistance (aim 2); and that HIV genotypes from patients experiencing failure of dolutegravir-based ART are associated with phenotypic resistance. We further hypothesise that these mutations develop along pathways specific to each HIV-1 subtype and, in combination, may compensate for the fitness costs of resistance mutations, that is, restore replication capacity compared with single mutations (aim 3).

## Methods and analysis

DTG RESIST is a multicentre study enrolling PWH from sub-Saharan Africa, Asia, and South and Central America. Figure 1 summarises the study design. PWH who experience virological failure in routine care (confirmed or based on a single measurement) are enrolled in a dedicated study visit. At the study visit, they provide informed consent and a blood sample, which undergoes sequencing if the VL is above 1000 copies/mL. The DTG RESIST data are linked with the routine data collected within the IeDEA.

**Figure 1 F1:**
[figure not shown]
Schematic representation of enrolment, specimen collection and sequencing. DBS, dried blood spot; VL, viral load.

### Setting

DTG RESIST is embedded within IeDEA. Established in 2006 by the National Institute of Allergy and Infectious Diseases, IeDEA is a global cohort collaboration that collects HIV/AIDS data from HIV care and treatment programmes. Six of the seven IeDEA regions participate in DTG RESIST: Southern Africa, East Africa, Central Africa, West Africa, Asia–Pacific, and the Caribbean, Central and South American region. The IeDEA consortium has been described in detail elsewhere.^17^,^19^
Figure 2 shows the countries participating in DTG RESIST, the HIV-1 subtypes and the Circulating Recombinant Forms (CRFs) prevalent in the region.

**Figure 2 F2:**
[figure not shown]
Countries with sites participating in DTG RESIST with the dominant HIV-1 subtypes and circulating recombinant forms. The colours represent the six IeDEA regions. IeDEA, International epidemiology Databases to Evaluate AIDS.

### Study population, eligibility and recruitment

DTG RESIST enrols adults and adolescents (age 10–19 years) living with HIV who have been on dolutegravir for at least 3 months and experience virological failure during routine care, defined as a single or, if available, a confirmed VL >1000 copies/mL on any dolutegravir-based combination ART regimen (figure 2). At enrolment, written informed consent is obtained from the participant or the parents or caretaker, as per local regulations. Key clinical and demographic data are collected using the Research Electronic Data Capture system.^20^ The DTG RESIST data will be combined with the clinical and epidemiological data prospectively collected within IeDEA.^17^,^19^

### Specimen collection and transport

Specimen collection and processing are performed according to WHO/HIVResNet guidance.^21^ Whole blood is collected from participants in EDTA tubes. Specimens are kept at room temperature (15°C–30°C) until centrifugation and separation (within 6 hours). All initial processing, centrifugation, pipetting and aliquoting will follow standard laboratory biosafety precautions at a local laboratory equipped to manipulate infectious clinical specimens. Following separation, 4×1.5 mL plasma cryovials from each participant will be frozen at −80°C. Two dried blood spot (DBS) cards with five spots each are also collected and stored at −20°C. In sites where storage of plasma samples is not possible, only DBS cards will be prepared^22^ (figure 1). A courier service experienced in transporting clinical specimens ships plasma and DBS specimens on dry ice to the genotyping labs in Durban, Mexico City or Bangkok.

### Sequencing and phenotypic resistance testing

The KwaZulu-Natal Research Innovation and Sequencing Platform in Durban, South Africa,^23^ the Centro de Investigación en Enfermedades Infecciosas (CIENI), Mexico City^24^ and the HIV-NAT virology lab at Chulalongkorn University, Bangkok, Thailand^25^ will serve as the regional laboratories. Whenever possible, whole HIV-1 genomes using the Illumina MiSeq Next-Generation Sequencing platform will be generated to examine mutations in genetic regions outside pol that could be associated with resistance to InSTIs (figure 1).^26 27^ Alternatively, if low virus loads do not allow whole viral genome sequencing, partial pol sequences, including the viral protease, reverse transcriptase and integrase genes, will be generated. We will perform phenotypic testing on about 100 selected samples focusing on non-B subtype viruses with major InSTI resistance mutations,^28^ including sequences with complex patterns of DRMs. Phenotypic resistance testing will be performed using the PhenoSense Integrase assay (Monogram Biosciences, San Francisco, California, USA^29^), which provides an in vitro measurement of the half maximal inhibitory concentration (IC50) to dolutegravir and the viral replication capacity. To test the reliability of genotypic prediction, we will compare the IC50 with the genotypic sensitivity scores predicted from the Stanford HIVdb, REGA or ANRS algorithms.^30^ We will use a viral Genome-Wide Association Study (GWAS) approach to explore the effect of mutations outside of the integrase.

### Outcomes and statistical analyses

We define two analysis populations to address aim 1 and aim 2: (1) all individuals who experienced virological failure on a dolutegravir-based first-line, second-line or third-line regimen in one of the participating cohorts and (2) all who started ART on a dolutegravir-based regimen or switched to such a regimen and were at risk of developing virological failure (the source population for (1)). The outcome of interest in population (1) will be any InSTI DRMs whereas in (2), it will be virological failure as defined above.

We will analyse population (1) using random-intercept logistic regression and population (2) using parametric survival models,^31^ stratified by treatment programme or country to account for heterogeneity across sites. We will measure the time from the date of switching to DTG-based ART (or from 6 months after initiating DTG-based first-line ART) to the earliest onset of virological failure, date of death or date of last follow-up visit. Exposure variables include age, sex, type of dolutegravir-based ART (initiated first line, switched to first line, second line or third line), previous exposure to InSTI drugs, pre-existing resistance mutations (from HIV-1 genotypes or predicted by the approach described below), advanced disease (as indexed by CD4 count <200 cells/µL), exposure to rifampicin, a history of ART interruptions and VL monitoring coverage and frequency (using approaches used in previous analyses^32 33^). We will follow recommendations on the conduct and reporting of prognostic research, including the choice of variables for inclusion in models and the handling of continuous variables and non-linear relationships.^34^ Missing values will be imputed using multiple imputations, assuming data are missing at random.^35^

We will explore using conjunctive Bayesian network models to assess the mutational pathways of DTG resistance (aim 3).^36^,^38^ The order of mutation accumulation and interdependence between mutations (ie, whether the acquisition of one mutation is less or more likely in the presence of other mutations) will be inferred from the co-occurrence patterns of mutations. We will learn these models for each subtype separately to identify subtype-specific mutational pathways. In exploratory analyses, we will search for novel resistance mutations that may mediate treatment failure and assess the impact of previously proposed mutations, such as mutations outside the HIV-1 integrase.^39 40^ We will combine the genotype data generated in aim 1 with viral whole genome sequences from phylogenetically matched controls from the Los Alamos HIV sequence database. In this pooled dataset, we will use GWAS methodology (as implemented in the PLINK software^41^) to identify the amino-acid mutations associated with failure.

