DTG RESIST will generate whole HIV-1 genomes and develop robust laboratory procedures to amplify, sequence and assemble the genomes from the diverse set of HIV-1 strains obtained in the multiregional network.^27^ The spectrum of dolutegravir-selected mutations and their effects on phenotypic susceptibility in non-B subtypes is yet to be fully characterised. HIV-1 main group (group M) has diversified into nine subtypes (A–D, D–H and J–K), six subsubtypes (A1–A4 and F1–F2), multiple CRFs and thousands of unique recombinant forms.^58 59^ Most PWH are infected with non-B subtypes, but much of the evidence about ART outcomes and HIVDR is based on subtype B viruses from Europe and North America. HIV-1 subtype could influence treatment outcomes and the emergence of drug resistance.^60^,^62^ Finally, phenotypic testing of non-B subtype viruses with major InSTI resistance mutations and GWAS to explore the effect of mutations outside of the integrase will likely provide new insights into the relevant drug resistance pathways. Bayesian evolutionary models of accumulating mutations will be used to predict the expected genotype at treatment failure.^36^

There are also limitations to the approach. An important weakness is the lack of genotypic resistance data from before dolutegravir treatment for most participants. We considered collecting and biobanking samples from all people starting dolutegravir-based ART and then having paired samples from pretreatment and at the time of virological failure. However, this was not deemed feasible at most IeDEA sites. We will explore whether these missing baseline genotypes can be imputed by adapting models to predict expected resistance genotypes based on treatment and clinical history. Other challenges include the lack of harmonised data on adherence. There is uncertainty about the distribution of HIV-1 subtypes across sites, and the statistical power of the analyses of patterns and risk factors for dolutegravir resistance will be limited. We will consider pooling our data with those from other related studies to address these issues.^15^ The results of the GWAS and Bayesian network analyses may be subject to overinterpretation due to strong model assumptions and limited sample size. To avoid this, we will qualify these as preliminary and hypothesis-generating studies requiring validation.

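### Aim 2 asks who develops dolutegravir resistance on treatment, but resistance is modelled only among people who have already failed, which can attenuate, mask or reverse an association

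*Protocol article*

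**What the plan says.** Under Study aims and hypotheses, aim 2 combines resistance data with routine cohort data "to explore the factors associated with emergent dolutegravir resistance". The hypothesis is that NRTI resistance, earlier InSTI exposure, male sex, younger age, later-line ART or advanced disease, rifampicin and lack of routine viral load monitoring "are risk factors for virological failure and the development of dolutegravir resistance (aim 2").

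Under Outcomes and statistical analyses there are two populations. Population (1) is "all individuals who experienced virological failure on a dolutegravir-based first-line, second-line or third-line regimen in one of the participating cohorts". Population (2) is everyone who started or switched to such a regimen and was at risk; it is described as "the source population for (1"). The outcomes are then fixed: "The outcome of interest in population (1) will be any InSTI DRMs whereas in (2), it will be virological failure as defined above". So are the models: "We will analyse population (1) using random-intercept logistic regression and population (2) using parametric survival models". One exposure list is given, not split by population. No model has failure with resistance among people at risk as its outcome, and no step combines the two models.

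The limitations in the Discussion cover missing baseline genotypes, adherence data, uncertain subtype distribution and limited power. They do not mention conditioning on failure.

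**The concern.** The hypothesis is about people taking dolutegravir: does a factor make it more likely that they end up with resistant virus? The population (1) model answers a different question: among people who have failed, does the factor make a mutation more likely? Failure lies on the path between factor and outcome, and the comparison group within failures is people who failed without a mutation. A factor that brings about failure mainly by a route that selects no resistance, such as poor adherence, enlarges that comparison group and lowers the odds ratio, whatever it does to resistance itself.

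The population (2) model does not fill the gap. On the plan's figures most failures carry no InSTI mutation, so that model mainly describes determinants of non-resistant failure. If the population (1) odds ratio is reported as the answer to the hypothesis, a real risk factor can be missed, or a factor with no effect on resistance can be reported as protective.

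**Working it through.** **Inputs from Sample size and power calculations.** 1500 failures (900 first-line, 600 second- or third-line). Two-year failure risk of 10%, 20% and 30% by line. Share of failures with InSTI mutations of 1–3%, 10–20% and 20–30% by line. Expected resistant cases 84–157.

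**The plan's own figure first.** Let y be the number of third-line failures, which the article does not give (an assumption here).
- Low end: 900×0.01 + (600−y)×0.10 + y×0.20 = 69 + 0.1y.
- High end: 900×0.03 + (600−y)×0.20 + y×0.30 = 147 + 0.1y.
- At y = 140 these are 83 and 161. For y of about 125–147 both ends lie within 3% of 84 and 157, so the range is reproduced closely enough for this purpose.

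The share of failures without a mutation is 1 − 84/1500 = 94.4% to 1 − 157/1500 = 89.5%.

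**Identity.** Let R be the risk of resistant failure and N the risk of non-resistant failure. Among failures, the odds of a mutation are R/N. Comparing exposed with unexposed:

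OR among failures = (R₁/N₁)/(R₀/N₀) = RR_R / RR_N.

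The ratio for developing resistance among people at risk is RR_R alone.

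**Illustration (effect sizes assumed, not from the article).**

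| RR_N | RR_R (at-risk ratio) | OR among failures | Reading |
|---|---|---|---|
| 1.5 | 1 | 0.67 | no effect looks protective |
| 2 | 1 | 0.50 | no effect looks protective |
| 2 | 1.5 | 0.75 | risk factor looks protective |
| 2 | 2 | 1.0 | risk factor masked |
| 2 | 3 | 1.5 | risk factor attenuated |

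In absolute terms, take first-line failure of 10% with 2% of failures resistant: R₀ = 0.002, N₀ = 0.098. With RR_N = 2 and RR_R = 1, the exposed have R₁ = 0.002 and N₁ = 0.196. The resistant share falls from 2.0% to 0.002/0.198 = 1.0%, and OR = (0.002/0.196)/(0.002/0.098) = 0.50.

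**Would this reach significance?** Take RR_N = 2, RR_R = 1, and exposure prevalence q in the source population (assumed 20–50%). Exposure is then q among resistant failures and 2q/(1+q) among the others: 0.20 against 0.333 at q = 0.20, and 0.50 against 0.667 at q = 0.50. A two-sided 5% two-proportion z-test on 1500 failures finds the false protective association with probability 0.75–0.87 (84 cases) or 0.95–0.98 (157 cases).

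**The plan's own rates, line of therapy** (lower ends of the ranges paired together, then upper ends).

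| Contrast | RR_R | RR_N | OR among failures |
|---|---|---|---|
| 2nd vs 1st, low | 0.020/0.001 = 20 | 0.180/0.099 = 1.82 | 11.0 |
| 2nd vs 1st, high | 0.040/0.003 = 13.3 | 0.160/0.097 = 1.65 | 8.1 |
| 3rd vs 1st, low | 0.060/0.001 = 60 | 0.240/0.099 = 2.42 | 24.7 |
| 3rd vs 1st, high | 0.090/0.003 = 30 | 0.210/0.097 = 2.16 | 13.9 |

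Line of therapy is attenuated by a factor of 1.6–2.4 and keeps its direction.

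**Bearing on the power statement.** The article claims at least 80% power for odds ratios of 2 or more. That refers to the ratio among failures. If a factor also doubles non-resistant failure, an OR of 2 requires RR_R = 2×2 = 4.

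**The case against.** Four objections have weight.

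First, the plan has two models, and they can be read together. In the 10%/2% example with RR_N = 2 and RR_R = 1, failure rises by 0.198/0.100 = 1.98, the resistant share changes by 0.0101/0.020 = 0.505, and the product is 1.0, the correct at-risk ratio. So the information is partly there. But the article states no such step, and an effect from a parametric survival model does not simply multiply with an odds ratio from a random-intercept logistic model.

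Second, resistance given failure is a legitimate target. It suits aim 1, and the article speaks of exploring associated factors and cites guidance on prognostic research. This stands, and it is why the model should be kept. It does not make the estimate an answer to a hypothesis about developing resistance.

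Third, a reader might infer that the listed factors will look protective, or that all of them get the wrong sign. The documents do not support that. Reversal needs a factor that raises non-resistant failure more than resistant failure; the article gives no such effect sizes, and its own rates for line of therapy show attenuation only. A reader might also infer that adherence cannot be adjusted for at all. The Discussion says only "Other challenges include the lack of harmonised data on adherence", and a history of ART interruptions, a partial proxy, is among the exposures.

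Fourth, an at-risk analysis has its own weakness. Sequencing requires enrolment and a viral load above 1000 copies/mL at the study visit, so people who have resuppressed are not genotyped, and genotyping may depend on adherence. This stands. It is a reason to place the new analysis beside the planned one and not in its stead.

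**Conclusion.** The concern holds in a limited form. The outcome assigned to each population does not match the part of the aim 2 hypothesis that concerns development of resistance. Reported as it stands, the population (1) odds ratio can attenuate, mask or reverse the at-risk association for factors that act largely through non-resistant failure. With an assumed doubling of non-resistant failure it is half the at-risk ratio; for line of therapy on the plan's rates it is smaller by a factor of 1.6–2.4.

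The identity itself needs only that each failure is either resistant or not. The sizes for other factors rest on assumed effects, and the significance probabilities also on assumed exposure prevalence and an unadjusted test. The documents do not show that any particular hypothesised factor will be reversed, nor that the population (1) model is invalid for its own question.

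**What to change.** 1. Keep the population (1) logistic model, label its result as InSTI mutations given virological failure, and do not report it as the risk of developing resistance.
2. Add a population (2) analysis with failure with InSTI mutations and failure without as separate event types, using cause-specific parametric survival models in the planned framework.
3. Handle failures that were not genotyped by inverse-probability-of-genotyping weights or by the multiple imputation already planned, with a sensitivity analysis for departures from that assumption.
4. State that the two results are interpreted together, and add conditioning on failure to the limitations.

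The cost is analysis time: the study data are already to be linked with the cohort data. The added analysis relies on genotyping being explained by recorded covariates, although enrolment and the study-visit viral load decide who is sequenced. It has the same few resistant events (84–157), so the number of covariates stays limited. And because most participants have no genotype from before dolutegravir, its event is failure with a mutation present, not proven emergence on treatment, and should be described so.

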### Sample size and power calculations

Based on a survey of participating sites and recruitment so far, we estimate that about 1500 PWH will experience virological failure, including 900 on first-line and 600 patients on second-line or third-line ART. The number of individuals with DRMs will depend on the distribution across groups of patients initiating or switching to different lines of dolutegravir-based ART, the proportion switching with detectable VL and other factors.

For aim 1, we will have reasonable power to detect differences between HIV-1 subtypes. For example, comparing subtype C with subtype B and assuming a total sample of 250 in each group will allow us to detect a difference in the prevalence of resistance mutations of 3% vs 9% with 81% power. The test statistic used for these calculations (done in PASS 15^42^) is the two-sided Z-Test; the significance level of the test is 0.0500. The power will be lower for comparisons with other subtypes with fewer patients. For aim 2, with 1500 patients, we will have ample power to identify risk factors for virological failure in univariable and multivariable models. Power will be more limited for analyses of factors associated with the presence of InSTI DRMs. Assuming that 10% of patients on first-line ART, 20% on second-line ART and 30% on third-line ART will develop virological failure within 2 years, and further assuming that among patients failing first-line ART 1%–3% will develop InSTI DRMs, whereas 10%–20% of patients failing second-line and 20%–30% of patients failing third-line ART will develop InSTI DRMs, we can expect 84–157 patients with InSTI DRMs. As shown in figure 3 (from PASS 15^42^), in univariable analyses, we will have a power of 80% or above to detect risk factors with an odds ratio of 2 or above for a range of exposure prevalence.^43^ Power will be lower in the multivariable models, which should not include more than 5–10 variables.^44^

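### Stratifying by country alone would not account for heterogeneity across sites, and would understate standard errors for risk factors that vary mainly between programmes, chiefly viral load monitoring

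*Protocol article*

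**What the plan says.** Under Outcomes and statistical analyses, the protocol article states: "We will analyse population (1) using random-intercept logistic regression and population (2) using parametric survival models". The sentence goes on to say that the analysis is "stratified by treatment programme or country to account for heterogeneity across sites". Programme and country are offered as alternatives, with no rule for choosing between them. The level of the random intercept in the logistic model is not stated.

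The exposures listed in the same section include "a history of ART interruptions and VL monitoring coverage and frequency". Study aims and hypotheses makes this a named hypothesis: "exposure to rifampicin and lack of routine VL monitoring are risk factors for virological failure", and also for the development of resistance. The Introduction says that recruitment takes place "in 17 countries in sub-Saharan Africa, South and Central America, and Asia". Under Sample size and power calculations, "we estimate that about 1500 PWH will experience virological failure", and 84 to 157 people with InSTI drug resistance mutations (DRMs) are expected. The article gives neither the number of programmes per country nor any intraclass correlation (ICC).

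**The concern.** Patients are nested in programmes, and programmes in countries. The sentence gives heterogeneity across sites as its purpose. A country stratum removes only differences between countries. If a country has several programmes, their patients share one baseline, and two patients of the same programme are treated as independent given country.

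This matters most for an exposure that is largely a property of the programme. VL monitoring coverage and frequency is the clearest case. If programmes differ in outcome for reasons outside the model, and the standard error ignores that variation, chance differences between programmes can be reported as an effect of monitoring.

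The other option has a gap of its own. With a separate baseline per programme, an exposure that is constant within a programme cannot be estimated at all. So neither option, taken as written, gives a sound test of the monitoring hypothesis.

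**Working it through.** **The plan's own figure.** The article states no figure that depends on the clustering level. Its 81% power for 3% vs 9% with 250 per group reproduces (80.8%, pooled two-sided Z-test) and has no bearing on this point.

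**Inputs from the article.** 17 countries; about 1500 failures (900 first line, 600 second or third line); 84 to 157 DRM cases, that is 84/1500 = 5.6% to 157/1500 = 10.5%; assumed 2-year failure risks of 10%, 20% and 30% by line.

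**Assumptions.** Programmes per country, between-programme variation within a country, and model-based standard errors.

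**Population 2 (time to virological failure).** The number at risk is 900/0.10 = 9000 plus 600/0.30 = 2000 to 600/0.20 = 3000, so 11,000 to 12,000; about 12,000 was used. The model was an exponential hazard stratified by country, with no true effect. Type I error at two-sided 0.05 for an exposure fixed at programme level, 3 programmes per country, from two simulations (1000 and 2000 datasets per setting):

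| SD of programme log-hazard | Simulated | Analytic check |
|---|---|---|
| 0.2 | 19%, 23% | 18% |
| 0.3 | 36%, 35% | 30% |
| 0.4 | 48%, 46% | 41% |
| 0.5 | 55%, 55% | 50% |

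The analytic check takes d = 1500/(17 × 3) = 29.4 events per programme. The variance of a programme's log rate is 1/d + SD², but the model counts only 1/d, so the variance is understated by a factor 1 + d × SD². At SD 0.2 this is 1 + 29.4 × 0.04 = 2.18, and 2 × (1 − Φ(1.96/√2.18)) = 18%. At SD 0.5 it is 1 + 29.4 × 0.25 = 8.35, giving 50%. The check agrees in direction and rough size, a few points below the simulations.

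Over 2, 3 and 5 programmes the simulated range is about 16% to 60%, with model standard errors 0.26 to 0.71 of the true SD. At SD 0 the rate is 4% to 6%, so programme variation is the cause. For a person-level exposure the rate depends on how far its prevalence differs between programmes: about 8% to 30% at an exposure ICC of 0.3, and about 6% to 15% at 0.1.

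**Population 1 (any InSTI DRM).** Simulated random-intercept logistic model, N = 1500, baseline prevalence 5.6% or 10.5%, country SD 0.5, binary programme-level exposure, 500 runs per setting, latent-scale ICC 0.02 to 0.10:

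| Programmes per country | Country intercept: SE / true SD | Country intercept: type I error | Programme intercept: type I error |
|---|---|---|---|
| 2 | 0.60 to 0.87 | 7.8% to 21.6% | 5.0% to 7.6% |
| 4 | 0.73 to 1.00 | 5.2% to 14.8% | 2.6% to 6.4% |

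At ICC 0 the country intercept gives 5.0% to 5.6%. For a patient-level exposure with the same prevalence in every programme, the SE ratio is 0.93 to 1.06. With one programme per country the two models are the same. Both then gave 8.0% and 12.2% in the two prevalence settings; as the models coincide, that excess cannot come from ignoring programme.

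**The case against.** **The plan does not choose country.** Programme is named first, and a condensed article may leave the exact stratum and variance estimator to an analysis plan that is not shown. This stands against any claim that the study will be analysed at country level, or that it is at fault for not naming a variance estimator. It does not remove the point: country is a stated option, it conflicts with the purpose given in the same sentence, and an analysis plan could adopt it and still comply.

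**The premise is inferred.** No programme counts are given. Offering the two levels as alternatives suggests that some countries have more than one programme, but the article does not say so. The size is therefore conditional.

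**Few exposures are affected.** A reader might infer that every listed risk factor is at stake. The calculations do not support that. Age and sex vary mostly within sites. Rifampicin exposure, advanced disease and line of ART are affected only as far as their prevalence differs between programmes.

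**The resistance analysis is less certain.** The level of its random intercept is unstated, and the stratification phrase fits the survival models most directly. A reader might also put an ICC of 0.05 into the design effect 1 + (m − 1) × ICC with m = 1500/51 = 29.4, which gives 2.42 and a type I error of 21%. That formula needs an observed-scale ICC. At 5.6% to 10.5% prevalence, a latent ICC of 0.05 corresponds to about 0.010 to 0.017 observed, so the design effect is 1.28 to 1.48 and the error about 8% to 11%.

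**Country has a practical appeal.** With 3 programmes per country there would be 84/51 = 1.6 to 157/51 = 3.1 DRM cases per programme, too few for separate programme baselines. This is fair, but it argues for a random programme effect, not for leaving programme out.

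**Conclusion.** The point holds in a conditional form. Country as the only level does not achieve the stated purpose wherever a country has several programmes whose outcomes differ. With model-based standard errors, it makes the test of a mainly programme-level exposure anti-conservative. VL monitoring coverage and frequency is the exposure chiefly concerned, and it carries a named hypothesis.

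Under the assumptions above, type I error for such an exposure is about 16% to 60% in population 2. In population 1 it is about 5% to 22%, if the country level is used there too. The direction is firm. The size is not, because it rests on programme counts and variances that the article does not report; the lower end for population 1 is essentially nominal, and with one programme per country there is no inflation from this source. The documents do not support the stronger reading that the planned analysis is already wrong, or that its risk factor results in general would be unreliable.

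**What to change.** Do not use country as the only clustering level.

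- **Population 1:** a random intercept for treatment programme, with country as a further effect where the 84 to 157 DRM events support it.
- **Population 2:** a country-stratified baseline with a programme-level shared frailty, or programme-clustered robust standard errors. Keep programme-stratified baselines only for exposures that vary within a programme.
- **Reporting:** state the number of programmes per country, so that readers can judge how much the choice of level matters.

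The change takes a sentence or two of analysis wording and slightly more model fitting. It needs only each participant's programme, which the plan's own programme option already requires. The price is wider confidence intervals for exposures that vary mainly between programmes.
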